## Methods/Design

In this randomized controlled trial with a sample size of 268 participants (after accounting for 20% drop out, M-CT: 107, TAU: 107) we compare an internet-supported self-directed prevention of relapse program as part of a SMS based monitoring versus treatment as usual (TAU). This M-CT program is called *Depression Free*. The target population is a group at elevated risk of relapse and recurrence as identified in several guidelines (e.g. NICE) [11,12] that consumes a considerable amount of health care and for whom initial benefits of antidepressants (AD) may be wane off in the long run. Relapse rates rise with increasing numbers of previous episodes up to 70% in 5 years [12]. In our previous study, we observed up to 62% recurrences within 2 years [13].

Randomization will be undertaken by an independent researcher and will be stratified by the number of previous depressive episodes and type of care (i.e. care by a general practitioner versus care in a mental health center) will then be used for stratified randomization. Thereafter our researchers receive the participant number and the automatically random generated condition in the trial by email. For a Flow diagram of the assessment methods see Figure 1.

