### Sample size

With 107 in M-CT versus in TAU 107 participants per condition the trial will be powered to detect a difference of 20% in the cumulative incidence rate of relapse/recurrence with a 2 year follow-up in a 2-tailed test at the conventional alpha level of 0.05 and a power of (1-beta) = 0.80, while conservatively assuming that relapse/recurrence will occur in 50% of the cases. Allowing for a drop-out of 20% we need to include 268 participants at baseline.

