#### Primary outcome

Primary outcome is time until relapse or recurrence of depression in the experimental group relative to the control group over 24 months using DSM-IV-R criteria as assessed by the SCID at 3 months, 12 months and 24 months [20]. Co-morbidity with concurrent chronic somatic illnesses will be assessed using the NEMISIS somatic illnesses list [23]. Secondary outcome is symptom severity as measured with the Inventory of Depressive Symptomatology (IDS-R) [19] and number of relapses as assessed by the SCID [20]. For the economic evaluation we will use the EuroQoL (EQ-5D) to obtain a generic quality of life related outcome [30]. Cost data related to health care uptake will be sampled using the TIC-P [22]. Cost data stemming from production losses due to absenteeism and working less efficiently while at work will be collected with the specific modules from the TIC-P [22].

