### Analysis

Cox regression analysis (survival analysis) will be performed, including as covariates the stratification variables that will be used in randomization, i.e.: number of previous episodes and type of care (primary/secondary/no care). Analysis will be conducted by intention to treat, including all subjects randomized in the study, and per protocol, including only subjects satisfying protocol. Statistical significance will be set at *P *< .05.

Mixed-model analysis of variance (ANOVA) will be used for the other variables, including baseline values of the dependent variable as a covariate in all analyses. We shall use implicit and explicit cognitive measures and stress measures (daily hassles) to explore the extent to which they mediate relapse and recurrence during treatment and follow up.

For the economic evaluation the balance between costs and health outcomes will be compared across strategies using a societal perspective. Primary outcome measure: the number of depression-free days. Both short-term and long-term consequences will be compared. Additionally, Quality Adjusted Life Years will be used as outcome (see also Table 1).

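### The mixed models for the secondary outcomes name the baseline value as covariate but not the stratification factors, which can cost some precision

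*Protocol article*

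**What the plan says.** **Randomisation.** Methods/Design says that allocation "will be stratified by the number of previous depressive episodes and type of care". Care has two levels there, general practitioner and mental health centre. No block size or other restriction within strata is stated.

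**Primary analysis.** The Analysis section specifies Cox regression "including as covariates the stratification variables that will be used in randomization", and Appendix 1 repeats this. Both give type of care three levels: none, primary and secondary.

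**Other outcomes.** The next paragraph of the Analysis section turns to mixed-model ANOVA, which "will be used for the other variables, including baseline values of the dependent variable as a covariate in all analyses". No other covariate is named. These outcomes include the secondary outcome of symptom severity on the IDS, which Table 1 schedules at baseline and nine later time points. Appendix 1 does not mention the mixed model.

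**The concern.** The plan names covariates model by model and states the stratification rule for one model only. Restricted allocation within strata keeps stratum differences out of the treatment contrast. A model that leaves the strata out still counts those differences as residual error. Its standard error then exceeds the true sampling variability of the estimate, and its confidence intervals are wider than they need to be.

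At stake is some power and precision for symptom severity and the other repeated measures. The primary analysis is not affected, because its model already carries both factors.

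**Working it through.** **The plan's own figure.** The plan gives no power or sample size for any mixed-model outcome. Its only calculation concerns relapse, "in a 2-tailed test at the conventional alpha level of 0.05 and a power of (1-beta) = 0.80". Reading the 50% as the overall rate (60% versus 40%):

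- Uncorrected n = [1.960√(2 × 0.5 × 0.5) + 0.842√(0.6 × 0.4 + 0.4 × 0.6)]² / 0.20² = 96.9 per arm.
- With continuity correction: (96.9/4) × [1 + √(1 + 4/(96.9 × 0.20))]² = 106.7, so 107 per arm.
- With 20% dropout: 214/0.80 = 267.5, so 268.

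This reproduces the stated numbers but does not bear on the secondary models. Below, 214 serves only as a scale.

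**Inputs.** Two-sided alpha 0.05 is from the plan. The share R of residual variance that the two factors explain after baseline adjustment is not in the documents, so 0% to 10% is assumed. The 80% starting power is also assumed for these outcomes.

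**Case 1: allocation balanced within strata, factors left out of the model.**

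- Reported SE / true SE = 1/√(1 − R)
- True alpha = 2[1 − Φ(1.960/√(1 − R))]
- Power = Φ(2.802 − 1.960/√(1 − R)), where 2.802 = 1.960 + 0.842 corresponds to 80% in the adjusted model
- Participants lost, in power terms = 214 × {1 − [(1.960 + z)/2.802]²}, where z is the normal quantile of that power

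| R (assumed) | SE ratio | True alpha | Power | Participants of 214 |
|---|---|---|---|---|
| 0% | 1.000 | 5.0% | 80.0% | 0 |
| 2% | 1.010 | 4.8% | 79.4% | about 3 |
| 5% | 1.026 | 4.4% | 78.5% | about 8 |
| 10% | 1.054 | 3.9% | 76.9% | about 16 |

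For R = 10%: 1.960/√0.90 = 2.066; 2.802 − 2.066 = 0.736; Φ(0.736) = 76.9%; 214 × [1 − (2.696/2.802)²] ≈ 16.

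**Simulation of case 1.** The set-up was 214 participants, 2 × 2 strata, permuted blocks of 4 (assumed), a single follow-up adjusted for baseline, and 4,000 runs per setting. At R = 10% the model without strata reported a mean SE of 0.1370 against an empirical 0.1307, a ratio of 1.05. The rejection rates are noisy: their Monte Carlo standard error is about √(0.05 × 0.95/4,000) = 0.3 percentage points. They were 5.1%, 4.1% and 4.6% without strata at R = 2%, 5% and 10%, and 5.4%, 4.6% and 5.7% with strata. At an extreme R = 20% the pattern is clear: 2.6% without strata and 5.0% with them.

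**Case 2: unrestricted allocation within strata.** In the same simulation the model without strata rejected in 4.7% to 5.2% of runs under the null, so it is valid. It is less precise: at R = 10% the empirical SE was 0.1386 without strata and 0.1319 with them, again a ratio of about 1.05.

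**The case against.** **The text says including, not only.** A reader might infer that the mixed model adjusts for the baseline value and nothing else. The wording does not say so, and nothing in it excludes the strata. An article may also leave the full covariate list of a secondary model to a fuller plan. This stands as a limit on the wording. It does not remove the point, because the same construction introduces the Cox covariates, where the strata are named. The Analysis section is the only description of the mixed model shown, and it states a different covariate from the one given for the primary model.

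**The consequence is conditional.** A reader might also infer that the standard errors are certainly too large. That needs two things which the documents do not establish. One is balanced allocation within strata. This is usual when a trial stratifies, but no restriction is stated. The other is prognostic value left after baseline adjustment. Methods/Design says "Relapse rates rise with increasing numbers of previous episodes up to 70% in 5 years", but that concerns relapse, not IDS severity given baseline IDS. If no prognostic value is left, the effect is zero. This objection stands in full.

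**The size is easily overstated.** Multiplying R by 214 gives about 4, 11 or 21 participants, but for balanced allocation that describes interval width. The power losses in the table correspond to about 3, 8 and 16. The simulation also used one follow-up rather than the planned repeated measures, so it confirms the mechanism and not an exact size.

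**Dropout.** One could argue that the strata make the missing-data assumption of the mixed model more credible, given the 20% dropout allowed for. No passage says that dropout depends on care setting or episode history, so the point does not rest on this.

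**Conclusion.** The point holds as a minor improvement for the secondary outcomes. The stated mixed model does not name the factors by which the trial randomises, although the stated Cox model does. With balanced allocation and factors that stay prognostic, the unadjusted tests are conservative. Over an assumed 0% to 10% of residual variance, the standard error is overstated by 0% to 5.4%, true alpha lies between 5.0% and 3.9%, and a nominal 80% power falls to no less than 76.9%. With unrestricted allocation the tests keep their level and only precision is lost. In neither case are false positives inflated, and the primary analysis is unaffected. The documents do not support a claim that the strata were deliberately excluded or that the reported standard errors will certainly be wrong.

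**What to change.** State in the Analysis section and in Appendix 1 that the mixed models include number of previous episodes and type of care as fixed effects alongside the baseline value, coded as actually used in the randomisation.

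The levels of type of care must be reconciled first. Methods/Design gives two, while Analysis and Appendix 1 give three, so the mixed models cannot at present follow both the randomisation coding and the Cox coding. The text should say which levels the randomisation used, including where participants without care were placed, and both models should then use that coding.

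The cost is a sentence or two and a check of the randomisation records. No new data or patients are needed, because both factors have to be known at randomisation. If previous episodes has two categories (an assumption), the models lose two degrees of freedom with two care levels or three with three, which is negligible with 214 to 268 participants.

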## Discussion

Given the high prevalence of MDD and its recurrent character new minimal interventions are needed to prevent relapse and recurrence in depression. Internet-based interventions might be helpful in empowering patients to become their own disease managers in this lifelong recurrent disorder. This is, as far as we are aware of, the first study that examines the (cost) effectiveness of an E mental health program using SMS and mail monitoring of symptoms with therapist support to prevent relapse in remitted recurrently depressed patients. Attrition is a very common phenomenon in internet-based interventions, hopefully the therapist support in this intervention will reduce attrition rates, as suggested in the meta-analysis of Spek et al [9]. In addition, mediation variables will be examined to get more insight into the most effective ingredients of the M-CT used. This might lead to insights that will lead to the development of more targeted interventions.

In summary, given the highly recurrent nature of MDD, new minimal interventions should be developed and evaluated to prevent recurrence in patients at high risk of recurrence, i.e. patients with multiple prior episodes. Internet based intervention including SMS based monitoring might be promising in disrupting the rhythm of depression, as will be examined in this study. This combination of self management-monitoring and self help could be an easily implemented and potential cost effective part of a broader disease-management program of a chronic (recurrent) illness, i.e. MDD.

## Appendix 1: Statistical Analysis Plan

All analysis will be conducted in agreement with the intention to treat principle as per the CONSORT statement. Cox regression analysis will be performed, including as covariates the stratification variables that will be used in randomization, i.e.: number of previous episodes, type of care (no/primary/secondary). Statistical significance will be set at P < .05. When adding the intervention to TAU is superior then the relapse/recurrence rate in this condition should be smaller than in the comparator condition (TAU alone). Therefore, we will obtain cumulative relapse/recurrence hazard rate ratios (Hr's). To gauge the robustness of the outcomes, the above analyses will be repeated under a completers-only framework.

Since co-morbidity with a concurrent chronic somatic illness for which medical attention is received is defined by the American Psychiatric Association as risk factor for future relapse and recurrence [10], differential response in this group of patients will be examined explicitly. Subgroups that show particularly good response to the intervention will be identified by regressing SCID depression severity on the interaction term of treatment and clinical characteristics of the participants as measured at baseline. Examples of other characteristics are number of previous depressive episodes, age at which the first depression occurred, concurrent personality disorders, concurrent anxiety disorder, experienced life events, some demographic characteristics (like gender) and sense of mastery. In addition, moderator analysis will also be conducted for demographic variables such as gender, age, educational level, partner status, employment status. These variables have been shown to be of prognostic value in depressive disorder. The same set of predictor variables will also be used in an incremental net benefit regression analysis to addresses the research question in what groups the intervention is likely to be particularly cost-effective.

The economic evaluation will be conducted both as a cost-effectiveness analysis with depression-free survival time as the clinical end term, and as a cost-utility analysis with incremental costs per quality adjusted life years (QALYs) gained as the clinical endpoint. For the latter, health-related quality of life, will be assessed with help of the EQ-5 D at baseline and follow-ups. Direct medical and direct non-medical cost data are collected with the TIC-P [22], a widely used health service receipt interview in economic evaluations. Unit resource use (GP visits, hospital days, etc.) will be multiplied by their appropriate integral cost prices [41]. Indirect non-medical cost data related to production losses through work loss days and work cutback days will be sampled with specific modules of TIC-P [22]. For the economic evaluation use will be made of the pertinent guidelines [42-44]. In other words, analyses will be conducted in agreement with the intention-to-treat principle, the societal perspective will be taken encompassing intervention costs, direct medical costs, direct non-medical costs and indirect costs. The latter will encompass production losses due to absenteeism and due to working less efficient while at work. Production losses will be economically valuated using the friction cost method [45] as per the Dutch guideline [42]. The time horizon will be set at two years and therefore costs and effects will be discounted. Costs and effects will be analyzed simultaneously, incremental cost-effectiveness ratios (ICERs) will be calculated and placed within 95% confidence intervals, 2,500 bootstrap replications of the ICERs will be projected on a cost-effectiveness plane, ICER acceptability curves will be plotted against different willingness-to-pay ceilings and sensitivity analysis will be conducted as a matter of course focusing on uncertainty in the analysis.

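### The primary Cox model is valid, but it could also prespecify baseline depressive severity and chronic somatic illness, for a probably small gain in power (optional)

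*Protocol article*

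**What the plan says.** Appendix 1 of the protocol article says that "Cox regression analysis will be performed, including as covariates the stratification variables that will be used in randomization". The Analysis section agrees and names the covariates as "number of previous episodes and type of care (primary/secondary/no care". Neither place lists any other covariate for time to relapse or recurrence.

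Other variables are available. Table 1 schedules the Hamilton scale, the IDS-SR and the list of somatic illnesses at T0. Appendix 1 says that concurrent chronic somatic illness "is defined by the American Psychiatric Association as risk factor for future relapse and recurrence". Trial objectives and Inclusion criteria make the same point, and Referral and recruitment plans targeted recruitment of these patients. Under Methods/Design, somatic illness is not a stratification factor. Appendix 1 uses it to look for differential response.

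For the remaining outcomes, the Analysis section plans mixed models "including baseline values of the dependent variable as a covariate in all analyses".

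The sample size is set for "a difference of 20% in the cumulative incidence rate of relapse/recurrence with a 2 year follow-up". Testing is two-sided at 5% and the target power is 80%. On the event rate, the same section reads "conservatively assuming that relapse/recurrence will occur in 50% of the cases".

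**The concern.** A Cox model that omits a prognostic covariate estimates a treatment hazard ratio closer to 1 than the ratio conditional on that covariate, and its test has somewhat less power. Here two candidate covariates are already collected, and the protocol calls one of them a relapse risk factor.

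The planned moderator work does not fill the gap. Appendix 1 describes it as a regression of SCID severity on treatment-by-characteristic interactions. That is a different outcome from time to relapse, and it leaves the headline hazard ratio unadjusted for somatic illness.

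At stake are some power and some protection against an unlucky allocation. If covariates are chosen only after an imbalance has been seen, the choice is data-driven. The time to name them is therefore before unblinding.

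**Working it through.** **1. The plan's own figure.** Inputs from Sample size: two-sided alpha 0.05, power 0.80, a 20-point difference and 50% relapse. Reading the 50% as the average of the arms gives 60% versus 40%.

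- Without continuity correction: n = [1.96·√(2·0.5·0.5) + 0.842·√(0.6·0.4 + 0.4·0.6)]² / 0.2² = 96.9, so 97 per arm.
- With continuity correction: n′ = (96.9/4)·[1 + √(1 + 4/(96.9·0.2))]² = 106.7, so **107 per arm**, as stated.
- Dropout: 214/(1 − 0.20) = 267.5, so **268**, as stated.

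**2. Power without further covariates.** With proportional hazards, HR = ln(0.6)/ln(0.4) = 0.557. Expected events are 107·(0.6 + 0.4) = 107. Schoenfeld power = Φ(√107/2·|ln 0.557| − 1.96), about 0.86. For two proportions without continuity correction, power at 107 per arm is 0.84. Both exceed 0.80.

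**3. Effect of adding the two covariates.** Cox simulation with 107 per arm, censoring at 24 months and 3,000 replicates per row. The marginal 24-month risks are held at the planned difference. *Assumed, because the documents give no values:* the hazard ratios in the first column and a 40% prevalence of somatic illness. The stratification variables are left out of both models because their effects are not given.

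| Assumed HR: severity per SD / somatic illness | 60% v 40%: power without → with | Change (points) | 50% v 30%: change (points) |
|---|---|---|---|
| 1.0 / 1.0 | 86.2% → 85.9% | −0.4 | −0.1 |
| 1.2 / 1.2 | 84.1% → 85.5% | +1.4 | 0.0 |
| 1.3 / 1.5 | 84.7% → 87.5% | +2.8 | +2.2 |
| 1.5 / 1.5 | 85.4% → 89.4% | +4.0 | +2.5 |
| 2.0 / 2.0 | 86.4% → 94.8% | +8.4 | +7.7 |

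Changes were taken before rounding. Monte Carlo error is about 0.6 points per power estimate. A second simulation with 60% versus 40% gave 83% to 87% power without the covariates, gains of about 0 to 3 points up to HR 1.5, and about 9 points when both were 2.0.

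**4. Where the gain comes from.** At 60% versus 40% the standard error of the log hazard ratio does not fall: it is 0.199 without the covariates and 0.200 to 0.202 with them. The estimate moves away from 1, from 0.555 to 0.541 in the third row and from 0.549 to 0.489 in the last.

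**5. Chance imbalance at 107 per arm.** The 95% range is ±1.96·√(2/107) = ±0.27 SD for a continuous covariate. For a binary covariate at the assumed 40% prevalence it is ±1.96·√(2·0.4·0.6/107) = ±13 percentage points. With an assumed HR of 1.5 per SD, an imbalance of 0.27 SD multiplies the hazard ratio by about 1.5^0.27 = 1.11, moving 0.557 to about 0.62 or 0.50.

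**6. Room in the model.** Treatment (1), episodes (taken as 1), care in three levels (2), severity (1) and somatic illness (1) make 6 terms. That leaves 107/6 ≈ 18 events per term.

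**The case against.** The strongest reply is that nothing here is an error. Adjusting for the stratification factors is a standard, prespecified choice, and the sample size does not rely on further covariates. The predictor best supported by the document, number of previous episodes, is already stratified and adjusted for: Methods/Design says relapse rates rise with it. Somatic illness is not ignored either, since differential response is planned. The document nowhere says that residual severity predicts relapse, and entry at a Hamilton score of 10 or less narrows its range. All of this stands, and it makes the change optional.

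Four stronger readings are tempting, and the documents do not support them:

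- *The trial loses up to 12 points of power.* That figure appears if 0.557 is fixed as the conditional hazard ratio and severity has a log hazard ratio of 0.7 per SD: 75.7% unadjusted against 87.3% adjusted. But the sample size plans a marginal difference in cumulative incidence. Fixing the conditional ratio makes the marginal effect smaller than planned (mean unadjusted HR 0.600), which itself lowers the unadjusted power.
- *The plan is inconsistent because other outcomes are baseline-adjusted.* Those models use the baseline value of the outcome itself. Time to relapse has none, as everyone enters recovered.
- *A chance imbalance would bias the result.* Under randomisation it would not; the confidence interval and p-value already allow for it. Prespecified adjustment only makes the estimate less sensitive to it.
- *Adjustment costs nothing.* It changes the estimand to a more conditional hazard ratio without lowering the standard error.

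It can also be said that 107 per arm understates the data. Intention to treat includes all those randomised, planned as 268, and dropouts contribute time until censoring. That is correct, and it makes a shortfall in power less likely.

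**Conclusion.** The point holds as a low-severity, optional improvement. The strata-only model is valid, no stated figure is wrong, and 80% power is met with 107 retained per arm. Adding the two covariates would gain about 0 to 4 points for hazard ratios up to 1.5, and about 8 to 9 points only if both are 2.0. If neither is prognostic, there is essentially no loss.

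These sizes rest on assumed prognostic strengths, an assumed prevalence, proportional hazards and the omission of stratum effects. If severity or somatic illness is correlated with the strata, the gain would be smaller. The case for somatic illness is the better supported, because it rests on the protocol's own statement. The case for severity rests on an assumption about prognosis.

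**What to change.** Before unblinding, specify the primary Cox model as treatment, the stratification variables, one baseline severity score (HRSD or IDS-SR total, chosen now and entered as continuous) and chronic somatic illness at baseline (yes/no, with the rule for deriving it from the somatic illness list written down). Report the strata-only model as a sensitivity analysis.

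This changes a line or two of analysis text and needs no new data. The hazard ratio becomes conditional on two more covariates, which the report should say.

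While that line is being edited, type of care should be reconciled. Methods/Design describes two levels for stratification (general practitioner or mental health center), whereas the Analysis section and Appendix 1 use three.

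### A completers-only repeat is a poor gauge of robustness for time to relapse, and it is neither defined nor reconciled with the per-protocol analysis named elsewhere

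*Protocol article*

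**What the plan says.** The Analysis section of the protocol article names two analyses of the Cox model: "Analysis will be conducted by intention to treat, including all subjects randomized in the study, and per protocol, including only subjects satisfying protocol". Appendix 1 opens with a general rule, "All analysis will be conducted in agreement with the intention to treat principle as per the CONSORT statement", and then gives a different companion analysis a stated purpose: "To gauge the robustness of the outcomes, the above analyses will be repeated under a completers-only framework". Neither section says who counts as a completer or as satisfying the protocol, or whether these are the same people.

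Appendix 1 mentions sensitivity analysis once more, but for the economic evaluation. The completers-only repeat is therefore the only analysis of time to relapse that the text labels as a check on robustness. On loss to follow-up, the Sample size section allows 20% overall with no split by arm, and the Discussion notes: "Attrition is a very common phenomenon in internet-based interventions".

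**The concern.** The ITT Cox model treats a participant who leaves without a recorded relapse as non-informatively censored. That is the assumption a robustness check should vary. Removing those participants does not vary it. It replaces a randomised comparison with one between groups selected after randomisation.

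The selection may also remove known outcomes. The SCID is scheduled at 3, 12 and 24 months, so a participant with a relapse confirmed at month 3 or 12 who misses month 24 has a complete time-to-event outcome. The ITT model counts that relapse. A set limited to people who finish follow-up does not.

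The undefined term matters too. Finishing follow-up can fail in either arm, whereas finishing the eight online modules can fail only in M-CT. These readings remove different people and can give different answers. At stake is the weight put on the robustness statement: a completers result close to the ITT result, or more favourable than it, would say little about whether drop-out has distorted the comparison.

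**Working it through.** **Inputs from the documents.** 107 per arm, 20% drop-out and 268 randomised (134 per arm), with relapse in 50% (Sample size); SCID at 3, 12 and 24 months (Primary outcome). **Assumed, not in the documents:** how drop-out depends on relapse in each arm.

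**The plan's own figure.** The section plans to "detect a difference of 20% in the cumulative incidence rate of relapse/recurrence with a 2 year follow-up"; the test is two-sided at 0.05, and power is 80%. Read the 50% as the average of 60% and 40%:

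- n = [1.96·√(2·0.5·0.5) + 0.8416·√(0.6·0.4 + 0.4·0.6)]² / 0.20² = 1.969² / 0.04 = 96.9.
- With continuity correction: (96.9/4)·[1 + √(1 + 4/(96.9·0.20))]² = 106.7, so 107 per arm.
- 214 / 0.80 = 267.5, so 268.

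The sample size reproduces and is not in dispute.

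**Relapses lost if a completer is someone who reaches month 24.** With drop-out unrelated to relapse and relapses recorded before leaving, 134 × 0.5 × 0.2 = 13.4 per arm. This loses information but causes no bias (simulated hazard ratio, HR, 1.00).

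**Bias when drop-out is linked to relapse only in M-CT, with no true effect.** Let a and b be the M-CT drop-out among relapsers and non-relapsers. Relapse among M-CT completers is p = 0.5(1−a) / [0.5(1−a) + 0.5(1−b)]. In TAU 20% of both leave, so relapse among completers is 0.40/0.80 = 50%. Then HR = ln(1−p)/ln(0.5). Overall drop-out is held at 20% per arm.

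The last three columns come from 10,000 simulated null trials per scenario (134 per arm, frailty variance 0.5, two-sided log-rank test at 0.05). Relapsers leave after the relapse is recorded, and other leavers are censored at departure. The nominal rate of false significance in favour of M-CT is 2.5%.

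| Ratio a:b | a / b | p | HR, formula | HR, simulated | False result for M-CT, completers | Same, ITT |
|---|---|---|---|---|---|---|
| 1.5 | 24% / 16% | 0.38/0.80 = 47.5% | 0.93 | 0.93 | 5.3% | 2.9% |
| 2 | 26.7% / 13.3% | 0.367/0.80 = 45.8% | 0.88 | 0.89 | 9.0% | 3.7% |
| 3 | 30% / 10% | 0.35/0.80 = 43.75% | 0.83 | 0.84 | 14.1% | 4.0% |

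**Where the bias vanishes, reverses or grows.**

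- Ratio 2 or 3 in both arms alike: completers HR about 1.00, false result for M-CT 2.5% to 2.6%.
- M-CT relapsers half as likely to leave (13.3% / 26.7%): p = 0.433/0.80 = 54.2%, HR = ln(0.458)/ln(0.5) = 1.13, against M-CT. A two-proportion check gives 0.5% false results for M-CT and 9.3% in total.
- M-CT drop-out of 30%, above the planned 20%, with TAU at 20%: ratios 1.5 to 3 give HR 0.89 to 0.73 and 8.3% to 31.7%, against 2.0% to 3.5% under ITT.

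**Effect of the definition.**

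- If an observed relapse counts as a complete outcome, the 30%/10% example becomes 0.50/0.95 = 52.6% in M-CT and 0.50/0.90 = 55.6% in TAU. HR = ln(0.474)/ln(0.444) = 0.92 instead of 0.83.
- If a completer is someone who finishes the modules, only M-CT participants are removed. Non-completion of about 20%, 35% and 50%, rising with underlying relapse risk, gives HR 0.90, 0.80 and 0.72 and false results of 8.2%, 20.0% and 34.3%. If non-completion is unrelated to risk, HR is 1.00.

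**ITT in the drop-out scenarios with 20% or 30% M-CT drop-out.** HR 0.97 to 1.04, total type I error 4.6% to 5.6%. The simulation omits the stratification covariates and the interval censoring that comes from three SCID visits.

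**The case against.** The strongest reply is that ITT is the lead analysis in both sections, so the trial's main error rate is untouched. That stands, and the simulation supports it.

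A second reply is that losing observed relapses depends on a definition that the article does not give. That also stands: if an observed relapse counts as a complete outcome, none is lost and the bias shrinks, though in the 30%/10% example it does not disappear. Likewise, with both terms undefined, nobody can say that the completers and per-protocol sets differ, only that the text does not reconcile them.

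Third, the documents give no drop-out by arm and no link between drop-out and relapse. Having an online programme to abandon is weak evidence of such a link: the Withdrawal section separates leaving treatment from leaving the study, and the Discussion hopes that therapist support will reduce attrition.

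A reader might infer that the completers analysis will favour M-CT, or that ITT and completers would agree while both are wrong. Neither is supported. The direction depends on an unknown mechanism. In the scenarios with bias, ITT stays near the null while completers-only moves away, so the two would tend to disagree. The simulation does not examine relapses that occur unrecorded after drop-out, so it cannot show joint bias.

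Finally, an article may leave missing-data detail to a fuller plan. The point does not rest on that omission. It rests on the purpose that Appendix 1 assigns to an analysis unsuited to it.

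**Conclusion.** The concern holds in limited form. Appendix 1 assigns the robustness check to an analysis that conditions on post-randomisation behaviour and does not test the censoring assumption. The Analysis section names a different, equally undefined set. That much needs no assumption beyond the text.

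The size is conditional. With 50% relapse, no true effect and 20% drop-out per arm linked to relapse only in M-CT, the completers HR of about 0.93 to 0.84 and the 5% to 14% false results for M-CT are illustrations of what could happen, not predictions. They require completers to mean people who finish follow-up and a drop-out mechanism that differs by arm. The primary ITT conclusion does not depend on this point. It is an inexpensive improvement to the plan and does not threaten the trial's validity.

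**What to change.** In Appendix 1, replace the completers-only repeat as the gauge of robustness with a sensitivity analysis in all randomised participants that keeps every observed relapse and varies the relapse hazard after drop-out. One workable form is multiple imputation of event times from baseline covariates and the IDS-SR scores available up to drop-out, with the post-drop-out hazard in M-CT multiplied in steps (for example 1.25, 1.5 and 2) until the conclusion changes.

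In both the Analysis section and Appendix 1, use one defined per-protocol or completer set, count participants with an observed relapse as having a complete outcome, and label the analysis supplementary to ITT.

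The cost is some wording and a little programming, with no new data collection, since the IDS-SR is already scheduled every three months. The limit is that IDS-SR data also stop for people who leave the study, so the imputation leans on earlier scores and on the stated multipliers.
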